## **PART II**

### **GUIDE TO RESEARCH PROPOSAL**

Please use the following guidelines to describe your research protocol on separate sheets, succinctly, but with sufficient information to allow evaluation by an expert consultant in your field. Use the following headings. A Sponsor protocol or grant can be substituted.

#### **1. SPECIFIC AIMS.**

**To better define the extent of damage and sparing of specific neural circuits after spinal cord injury (SCI). To compare the efficacy of an exercise training regimen simultaneously targeting brainstem and corticospinal circuits to a traditional treadmill training regimen in a population of chronic SCI participants.**

#### **Observational Phase: Functional and electrophysiological assessment of residual circuitry in chronic spinal cord injury (SCI)**

- A. Functional Assessments:** sensory and lower extremity motor scores on American Spinal Injury Association Impairment Scale (AIS); Berg Balance Scale; modified Ashworth Scale; Spinal Cord Assessment Tool for Spasticity (SCATS); Walking Index for Spinal Cord Injury II (WISCI II); 10-meter walk test (ambulatory Participants only); steps taken on the 10-second Step Test (AIS C/D Participants only); grasp-and-release test (cervical-level participants only); pinch dynamometry (cervical-level participants only) Spinal Cord Injury Spasticity Evaluation Tool (SCI-SET); WHOQOL-BREF and SCIQoL quality of life questionnaires; and the McGill Pain Questionnaire (short form).
- B. Electrophysiological Assessments:** Motor evoked potentials; H-reflex testing; seated and standing dynamic posturography; and quality of coordinated muscle activation assessed by surface electromyography.

#### **Interventional Phase: Targeted exercise training for motor-incomplete thoracic SCI**

- A. Interventions:** Participants with motor-incomplete SCI (AIS grade C or D or volitional strength of at least 1/5 in two or more key lower extremity muscles, AND volitional strength of at least 3/5 in shoulder and elbow muscles) or some participants with electromyographic evidence for residual motor circuits will undergo two different exercise training regimens in random order: conventional locomotor treadmill training and multimodal training combining balance training with skilled hand exercises. A harness and two clinicians will be used for support and safety.
  - 1. **LOCOMOTOR:** harness-supported treadmill training.
  - 2. **MULTIMODAL:** staged balance training (to stimulate brainstem postural circuits) plus skilled hand exercises (to simultaneously stimulate corticospinal circuits);
- B. Schedule:** Training sessions of 30 minutes will occur 3-4 times per week for a total of 48 sessions per intervention. The functional and electrophysiological parameters described in Phase 1 will be assessed at the beginning and end of each training period; and 6 weeks after completion of all training.
- C. Primary Outcomes:** Change in tibialis anterior motor evoked potential amplitude; change in lower extremity motor score.
- D. Secondary Outcomes:** Change in AIS sensory score; change in Berg Balance Scale score; change in number of steps taken during Ten Second Step Test; change in gait speed and disability; change in leg spasticity (modified Ashworth Scale, SCATS, and SCI-SET); change in grasp-and-release test or pinch dynamometry (in cervical-level participants); change in pain (McGill Pain Questionnaire); change in quality of life (WHOQOL-BREF and SCIQoL) change in upper and lower extremity lean tissue mass; change in soleus H-reflex facilitation; change in seated and standing posturography; and change in motor control measured by surface electromyography.

We hypothesize that in motor incomplete SCI participants, combinations of exercises simultaneously stimulating corticospinal and brainstem tracts *above* spinal lesions should lead to greater neural recovery *below* lesions than traditional treadmill training.

**Please note:** The training protocols described in this proposal involve interventions and safety mechanisms that are similar to other clinical and research protocols already in extensive use both in our SCI rehabilitation service and our SCI Center of Excellence. Therefore, the risks of the training intervention are not expected to be larger than those of standard SCI rehabilitation or our other research protocols such as the Lokomat and ReWalk protocols.

Diagnostically, this protocol introduces several assessment techniques that are new to our center – three of these techniques, computerized posturography, surface electromyography, and H-reflex facilitation testing, do not pose significant new risks. One of these techniques, motor evoked potentials, involves transcranial magnetic stimulation (TMS) – the risks of this procedure, and the extensive safeguards we will use, will be extensively discussed.

## 2. BRIEF REVIEW OF RESULTS OF OTHERS AND CURRENT STATE OF KNOWLEDGE

### The spared fibers of spinal cord injury

Traumatic spinal cord injury (SCI) only rarely leads to complete cord transection – most injuries occur through external trauma to the spinal column, leading to varying degrees of cord contusion (NSCISC 2013). Therefore, rather than severing the cord, most injuries leave a portion of the cord's nervous tissue intact (Hayes & Kakulas 1997; Kakulas 1987). Even in patients who cannot consciously sense or move their body below a lesion, there is often some degree of motor, sensory, and/or autonomic circuit sparing (McKay et al. 2004; Sherwood et al. 1992).

[figure not shown]

**Figure 1** – Schematic of corticospinal (red) and brainstem tracts (green) after anatomically incomplete cervical spinal cord injury (A). Note that only brainstem fibers survive below the lesion. Repetitive simultaneous firing of CST and brainstem tracts (B-C) leads to strengthening of alternative connections between CST fibers and brainstem neurons. In this fashion, a detour pathway reforms between the cortex and motor neurons on the previously denervated side of the cord (D).

Spared circuits represent a potential pathway for recovery – therefore, it is crucial to characterize their identity in individual patients. Due to their anatomically diffuse distribution, fibers of brainstem and spinal tracts (for example, the reticulospinal tract) are much more likely to survive cord damage than those of cortically-originating tracts such as the corticospinal tract (CST) (Jankowska & Edgley 2006; Nathan et al. 1996).

If we were better able to detect and characterize spared neural pathways, clinicians could give patients not only a more accurate prognosis, but perhaps better treatment – that is, interventions more specifically targeted toward spared circuits could improve rehabilitation outcomes. This proposal presents the rationale, preliminary data, and research design intended to achieve these goals.

### Recovery through Rerouting, not Regeneration

To re-establish conscious control over brainstem and spinal circuits, treatments need to connect brain centers that initiate voluntary movement with the spinal centers that execute that movement (**Figure 1**). These types of rerouted detour connections mediate functional recovery in animal SCI models even without specific treatment (Bareyre et al. 2004; Courtine et al. 2008). We aim to improve this process.

## Fire together, Wire together

One approach to improving connectivity and function after CNS injury involves increasing activation of the nervous system itself. Activity-inducing treatments include repetitive transcranial magnetic stimulation (TMS), transcranial direct current stimulation (tDCS), and various forms of implanted electrical stimulation (Brus-Ramer et al. 2007; Carmel et al. 2010; Courtine et al. 2009; Harkema et al. 2011; Minassian et al. 2007; Sadowsky & McDonald 2009).

We propose to use a non-invasive method of neural activation – repetitive exercise training – to improve connectivity of the injured spinal cord. Our approach to exercise training for SCI builds on the principle of ‘Fire together, Wire together’ made famous by Donald O. Hebb (Hebb 1949): When nearby neurons repetitively fire in sequence, they are more likely to form new and/or stronger physiological connections.

The CST sends many collateral fibers toward brainstem nuclei as it descends toward the spinal cord (Jankowska & Edgley 2006; Matsuyama et al. 2004). We plan to strengthen these collateral connections by using targeted repetitive exercises that stimulate nerves from cortical and brainstem pathways simultaneously (**Figure 1**). We have begun demonstrating the feasibility of this approach in mouse models of central nervous system injury (Harel et al. 2010; Harel et al. 2013). We now intend to translate this approach to human patients.

## Data from other studies in human Participants

*Balance training on an unstable surface improves postural control in chronic thoracic SCI patients (Kim et al. 2010)* – In a small study that shares similarities with our proposed study, Kim et al. tested the effects of balance training in a chronic thoracic SCI population. Seven participants with motor-complete (AIS A or B) injury were subjected to progressively more difficult balance exercises over the course of 20 sessions. Balance training resulted in increased reaching distance and decreased postural sway relative

[figure not shown]

**Figure 2** – Balance training on an unstable surface improves reach and postural sway in chronic thoracic SCI patients. (A) Increased distance achieved on Modified Functional Reach Test (MFRT). (B) Larger reduction in sway area determined by computerized posturography. Adapted from Kim et al., 2010.

to patients receiving ‘conventional’ therapy (**Figure 2**). This demonstrates the effectiveness of a staged balance training program such as the one we propose to use in our participants, as well as the feasibility of tracking outcomes using computerized posturography. As detailed in the Research Design, we plan on utilizing a related balance training protocol with a greater number of participants, more finely differentiated control treatment, and more sensitive outcome measures.

*Detailed surface electromyography (EMG) recordings sensitively track improved patterns of motor control over time in SCI patients (McKay et al. 2010)* – McKay and colleagues have repeatedly shown the value of using surface EMG to glean information about residual neural connections and motor control after SCI. In this recent demonstration, they performed extensive EMG

[figure not shown]

**Figure 3** – Progressive improvement in electrographic motor control over various muscle movements in an individual SCI patient over time. Adapted from McKay et al., 2010.

evaluation on acutely injured patients 1 to 11 days post-SCI, then performed repeated assessments over the next 3-17 months. They were able to electrographically track progressive improvement in overall coordination and control of major

muscle groups over time (**Figure 3**). Importantly, this type of analysis tracks changes in *motor control* more sensitively than clinical examination or other types of assessments of *muscle movement*. We intend to continue developing this tool as a powerful biomarker for underlying changes in neural circuitry in response to various treatments.

### 3. PROCEDURES, METHODS AND EXPERIMENTAL DESIGN.

#### Participant Inclusion Criteria:

##### Phase 1 Functional and electrophysiological assessment of residual circuitry

1. Age between 21 and 65 years;
2. Chronic thoracic SCI (levels C2-T12; more than 12 months since injury);
3. AIS grades A, B, C, or D.

##### Phase 2: Targeted exercise interventions

1. Age between 21 and 65 years;
2. Chronic thoracic SCI (levels C2-T12; more than 12 months since injury);
3. AIS grades C or D or volitional strength of at least 1/5 in two or more key lower extremity muscles; or some participants with electromyographic evidence for residual motor circuits;
4. Strength of at least 3/5 in shoulder and elbow muscles;
5. Able to tolerate standing with support;
6. Morphologically capable of fitting a weight-support harness and robotic treadmill system: measurements of the greater trochanter to lateral epicondyle between 35-47 cm for placement in the thigh cuffs; pelvic width >50 cm; thigh circumference above the knee <57 cm; and body mass <135 kg.

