**Baseline testing (to be conducted over two visits):**

Once a participant has provided signed informed consent, a detailed review of the participant’s history and medical record will be conducted. A physical exam will be performed, including the Modified Ashworth Scale, the Spinal Cord Assessment Tool for Spasticity (SCATS) (Benz et al. 2005), and the American Spinal Injury Association (ASIA) Impairment Scale (AIS). Further clinical assessments will include the Berg Balance Scale; the Walking Index for Spinal Cord Injury II; the 10-meter walk test; the 10-second seated step test; a modified grasp-and-release test (Wuolle et al., 1994); pinch dynamometry; the Spinal Cord Injury Spasticity Evaluation Tool (SCI-SET) (Adams et al. 2007); the WHOQOL-BREF questionnaire (World Health Organization 1998); SCI-QoL questionnaire (Tulsky et al. 2011); and the

McGill Pain Questionnaire (short form). Depending on the severity of paraparesis, not all Participants will be able to perform the step or walk tests. As such, no baseline walking data will be collected for these outcomes in these participants. To ensure tolerance of upright position, heart rate and blood pressure will be measured for 10 minutes while the Participant is in an upright position supported using an overhead harness or standing frame. A full-body DXA scan will be performed. To be eligible for Phase 2 of the study, results from the DXA of the proximal femur must not have a T-score lower than 3.5SD below age/gender-matched controls. Seated and standing computerized posturography, motor evoked potentials, multiple tests of soleus H-reflex facilitation, and surface electromyography will also be assessed. At this point, the study evaluation is complete for participants with AIS A/B impairment. Only participants with AIS C/D injury or volitional strength of at least 1/5 in two or more key lower extremity muscles or some participants with electromyographic evidence for residual motor circuits will be eligible for the interventional component of our study. If any exclusion criteria are met, or if the participant decides at any time not to continue, he or she will not be further studied.

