### **Randomization:**

Participants with motor incomplete SCI will receive the two training interventions in randomized order, with randomization occurring in blocks of 6 subjects.

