### **Research Design:**

This protocol will investigate the efficacy of combining fine-motor exercises with balance exercises in the rehabilitation of chronic thoracic spinal cord injury patients. There are two phases: an observational phase for participants with either motor complete or incomplete SCI; and an interventional phase for participants with motor incomplete SCI. The observational phase will characterize the residual function of specific neural circuits. The interventional phase will employ a single-group, single-blinded, pre-post-intervention crossover research design. We plan to enroll 51 participants for the observational phase. 24 participants with motor incomplete SCI will continue with the interventional phase, lasting approximately 9 months. The protocol will take 3 years to complete. We hypothesize that participants will demonstrate improved neural connectivity when undergoing multimodal training compared to locomotor training.

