**All participants will undergo baseline testing. Only participants with motor-incomplete SCI (AIS C/D grades or volitional strength of at least 1/5 in two or more key lower extremity muscles AND volitional strength of at least 3/5 in shoulder and elbow muscles) will participate in the exercise training phase as well as the post-training and follow-up assessment testing.**

The following procedures will be used:

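### Phase 2 eligibility contradicts itself: an undefined EMG route admits people whom other sections exclude, and some of them may have a baseline LEMS at or near 0

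*Protocol*

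**What the plan says.** **Routes in.** The Phase 2 inclusion criteria in section 3, repeated in section 3a, accept AIS grade C or D, or strength of 1/5 or better in at least two key leg muscles, "or some participants with electromyographic evidence for residual motor circuits". Section 1 (Interventional Phase) offers the same third route: "or some participants with electromyographic evidence for residual motor circuits will undergo two different exercise training regimens in random order". So does Baseline testing: "or some participants with electromyographic evidence for residual motor circuits will be eligible for the interventional component of our study".

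**Restrictions.**
- Section 3a, in the paragraph just before the clinical tests, opens its rule with "Only participants with motor-incomplete SCI (AIS C/D grades or volitional strength of at least 1/5 in two or more key lower extremity muscles". It adds the arm-strength condition and has no EMG route.
- Randomization: "Participants with motor incomplete SCI will receive the two training interventions in randomized order".
- Research Design: "24 participants with motor incomplete SCI will continue with the interventional phase". The paragraph after the section 3a exclusion list repeats this.
- The hypothesis in section 1 begins "We hypothesize that in motor incomplete SCI participants".
- Baseline testing, one sentence before it admits the EMG route: "At this point, the study evaluation is complete for participants with AIS A/B impairment".

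**Limit on the route.** Both exclusion lists bar from Phase 2 anyone in whom no tibialis anterior MEP can be found at baseline, even with facilitation.

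**Outcomes.** The primary outcomes are change in tibialis anterior MEP amplitude and change in LEMS. Statistical Analysis expresses each outcome as a within-subject percent change over each intervention and compares the modalities with independent-sample tests.

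**The concern.** Eligibility should give one answer for one candidate. Here the answer depends on which section is read, and where the EMG route does appear, the word *some* leaves the decision to whoever is screening. No section names the EMG finding, the manoeuvre, the threshold or the decision-maker, and none sets a cap.

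Two things are at stake. First, the population randomised may be wider than the motor-incomplete population named in the section 1 hypothesis, by an amount that discretion sets. Second, people who need the EMG route have very little measurable leg strength, and LEMS is one of the two primary outcomes. A percent change needs a baseline that is not zero.

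**Working it through.** **1. Who needs the EMG route.** The three routes are alternatives, so the third matters only for someone who is not AIS C or D and does not meet the strength rule. Phase 1 enrols grades A to D, so that person is AIS A or B. The protocol's summary of an earlier balance-training study treats A or B as motor-complete. The EMG clause does not use that term, so this step is an inference from the protocol's own usage.

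**2. One candidate against each section.** Take an AIS B candidate with fewer than two key leg muscles at 1/5, adequate arm strength, a detectable tibialis anterior MEP and some leg EMG activity, who meets every other criterion.
- Inclusion lists in sections 3 and 3a, and section 1: may enter, if chosen as one of the *some*.
- Section 3a, paragraph before the clinical tests: may not enter.
- Randomization, Research Design, and the paragraph closing the section 3a exclusions: outside the population described.
- Baseline testing: finished by one sentence, possibly eligible by the next.

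The MEP exclusion does not settle this, because the candidate passes it. It tests conduction to one muscle and says nothing about which EMG evidence qualifies.

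**3. Baseline LEMS on this route.** Assume LEMS is the sum of the key-muscle grades, each out of 5, counted separately in each leg. Failing the strength rule means that at most one key muscle scores 1 or more. Baseline LEMS is then 0, or the grade of a single muscle, at most 1 × 5 = 5. By contrast, the strength rule guarantees at least 2 × 1 = 2.

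**4. The planned metric at such baselines.** Percent change = 100 × (end − baseline) / baseline.
- Baseline 0: division by zero, so no value exists, whatever the participant gains.
- Baseline 1, gain of 1 point: 100 × 1/1 = 100%.
- Baseline 20, gain of 1 point: 100 × 1/20 = 5%.

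The same one-point gain therefore counts 20 times as much in the second case as in the third.

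**5. The plan's own power figure.** Inputs from Power Calculation: 50% versus 25%, so a difference of 25; a stated variance of 25%, read as an SD of 25; two-sided α = 0.05; 18 subjects, each giving one value per modality. The noncentrality is (25/25) × √(18/2) = 3.0. Power is 0.83 by the t-test, or Φ(3.0 − 1.96) = 0.85 by the normal approximation. Enrolment is 18/(1 − 0.25) = 24. The statement of more than 80% power reproduces.

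**6. Illustration only.** Neither the number k of entrants without a usable LEMS value nor any LEMS effect size is in the protocol. Borrow the MEP assumptions for LEMS and let k of the 18 completers have no percent change. The noncentrality is √((18 − k)/2), and t-test power at α = 0.05 is:
- k = 1: 0.81
- k = 2: 0.78
- k = 4: 0.72
- k = 6: 0.65

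These figures show sensitivity to k. They do not estimate the loss in this trial.

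**The case against.** The best defence is that the EMG clause appears in both formal inclusion lists and in two other places, so the widening looks deliberate and the section 3a paragraph may simply not have been updated. The MEP exclusion is also an objective gate, so entrants must show corticospinal conduction to the leg. Both points are fair. They explain how the conflict may have arisen, but they do not remove it or turn *some* into a criterion. A separate analysis plan might handle zero baselines, but eligibility belongs in the protocol, and the percent-change metric is fixed there.

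Several stronger readings are tempting, and the documents do not support them:
- **Any AIS B candidate with a trace of EMG gets in.** The MEP exclusion also has to be passed.
- **The aim and planning study are confined to motor-incomplete injury.** The aim refers to chronic SCI, the planning study to incomplete thoracic SCI, and Research Design restates the hypothesis without the restriction. Among the statements of aim and hypothesis, only the section 1 hypothesis names motor-incomplete participants.
- **EMG-route candidates will be common.** The background says that some motor, sensory or autonomic sparing is often present. It does not say that leg EMG activity is common, least of all among people who also have the required MEP.
- **The LEMS difference shrinks by k/24** (2/24 = 8%, 4/24 = 17%, 6/24 = 25%). This assumes zero change in these entrants and an average that includes them. Under percent change, a baseline of 0 gives no value to average, and a baseline of 1 can swing by 100%, so the effect may be missing data or added variance rather than dilution.
- **The comparison of modalities is biased.** Selection precedes the random order and each participant is to receive both trainings, so discretion over entry does not in itself favour either one.

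Instability at low baselines is also not unique to this route. At the strength-rule minimum of 2, a one-point gain is already 50%. What the EMG route adds over the strength rule is the possibility of a baseline of 0.

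**Conclusion.** The point stands as a contradiction in eligibility that should be resolved. It rests on the text alone: four places open the EMG route, one closes it expressly, others describe a motor-incomplete population, and Baseline testing does both in consecutive sentences. Entry by the EMG route is discretionary because no qualifying evidence is defined.

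The consequence for LEMS follows from the protocol's own percent-change metric together with the assumption about how LEMS is summed. Its size cannot be stated, because the number of entrants and their baseline scores are not given. The randomised population may be wider than the one in the section 1 hypothesis, not wholly different from it. No harm to the MEP comparison is shown.

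**What to change.** Bring section 1, both Phase 2 inclusion lists, Baseline testing, Randomization, Research Design, the section 3a paragraph before the clinical tests and the paragraph closing the section 3a exclusions to one eligibility rule. Either the EMG route is absent everywhere, or it is present everywhere with one fixed criterion, applied to all candidates, in place of *some*. Amend the AIS A/B sentence in Baseline testing so that it does not close a route that remains open. Which option to take is the sponsor's choice.

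If the route is kept:
- record the entry route at randomisation;
- analyse LEMS as absolute change in points, so that a baseline of 0 is usable;
- prespecify a supporting analysis in participants who meet the section 3a rule without the EMG route;
- word the hypothesis and conclusion for the population actually randomised.

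Removing EMG-route participants from the primary set is not required. On the plan's assumptions it would cost the MEP comparison power, from 0.83 to 0.78, 0.72 or 0.65 if 2, 4 or 6 of the 18 completers were excluded without replacement.

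The cost is protocol wording, plus slightly narrower recruitment if the route is dropped or a little extra analysis if it is kept.
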